#### Additional Analysis: Non-adherence or Missing Data

We will further analyze if discontinuation affects more one of the experimental groups, and we will also evaluate the baseline properties of the subjects that discontinue or perform the intervention at a non-successful level (reaching a number of essays/training days). Missing behavioral data can be handled by multiple imputation. However, in the case of missing, uncompleted, or artifacted MRI data, we will discard these subjects from the group analysis.

Missed trainings will be addressed by an intention-to-treat (ITT) approach to evaluate if they affect the results. Thus, we will analyze the available data by list-wise deletion without imputing the unknown values.

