#### Connectivity Changes: MRI Assessment

All participants will undergo a 3T brain-MRI acquisition at baseline (T0), after treatment (T1), and after 12 months (T2). The scanning protocol will include structural and functional acquisitions. The MRI sequences will be the following: (1) high-resolution three-dimensional T1-weighted images acquired in the sagittal plane (MPRAGE sequence: TR = 2,400 ms, TE = 3.32 ms, TI = 1,000 ms, 256 slices, FOV = 224 mm; flip angle = 8°; 0.8 mm isotropic voxel); (2) 3D T2-weighted images in sagittal orientation (TR = 3,200 ms, TE = 298 ms, 256 slices, FOV = 224 mm; 0.9 mm isotropic voxel); (3) diffusion tensor imaging sequence (DTI) (single-shot diffusion-weighted EPI, *b* = 1,000 mm^2^/s, 30 directions, TR = 7,700 ms, TE = 89 ms, FOV = 244 mm; 2 mm isotropic voxel). Each direction will be acquired twice (AP and PA) and images will be averaged, improving signal-to-noise ratio; (4) resting state fMRI sequence (gradient-echo echo-planar imaging–EPI sequence) (240 volumes; 40 axial slices; TR = 2,500 ms; TE = 28 ms; FOV = 240 mm; flip angle = 80°; 3 mm isotropic voxel); (5) clinical sequences: a gradient T2 sequence (TR = 518 ms; TE = 20 ms; FOV = 240 mm; flip angle = 20°, voxel = 0.8 mm × 0.8 mm × 3 mm) and an axial FLAIR sequence (TR = 9,000 ms; TE = 96 ms; TI = 2,500 ms, FOV = 240 mm; flip angle = 150°, voxel = 0.9 mm × 0.9 mm × 3mm).

Brain plasticity will be assessed by computing brain connectivity through the analysis of DTI and resting-state fMRI sequences. It will be considered a primary measure. However, its analysis needs to be performed *post-hoc* with multiple comparisons' correction (FEW, FDR). Structural and clinical imaging (T1-, T2-weighted, and clinical sequences) are acquired to ensure that there are no significant baseline differences in brain structure between groups.

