#### Imaging Data

To compute brain connectivity and perform graph-theoretical analysis, we need to preprocess MPRAGE, fMRI, and DTI data sets altogether. Thus, we can perform structural (by probabilistic or deterministic tractography) and functional connectivity analyses, i.e., parcellating the brain into functionally related areas using an atlas [i.e., the AAL atlas by (59)]. The mean time series of the obtained regions' voxels can be used to calculate cross-correlations between them, thus obtaining an *n* × *n* correlation matrix that represents each subject's connectivity profile.

To do that, we will segment the MPRAGE images by the automated FreeSurfer stream (version 5.3; available at https://surfer.nmr.mgh.harvard.edu/) into different cortical regions. With FSL [FMRIB's Software Library, http://www.fmrib.ox.ac.uk/fsl/; tract-based spatial statistics (TBSS) and tractography Diffusion Toolbox (FDT)], we will analyze the DTI dataset. After individual FA map extraction, a probabilistic tracking algorithm is used to estimate white matter pathways connecting different regions of interest. Again, a general linear model, correcting for multiple comparisons across space, will be used to compare differences among groups. Finally, we will preprocess functional images (fMRI) using FSL and AFNI (Analysis of Functional NeuroImages, https://afni.nimh.nih.gov/). An independent component analysis (ICA) can be carried out using tensorial independent component analysis as implemented in MELODIC part of FSL. This enables to obtain a set of independent components and identify the common resting-state functional networks (60).

Brain plasticity will be assessed by *post hoc* analysis with a correction for multiple comparisons (FWE, FDR).

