## Details of the Sample Enrollment to Date

A total of 263 children and their families were contacted to participate in the study from the two areas covered by the two participating hospitals. From those, a total of 44 children and their families (16.73%) consented to participate in the study and underwent the first neuropsychological assessment. A total of 16 families are still pending on taking a decision regarding if participating or not; 100 did not meet the inclusion criteria, 65 families refused to participate in the study, and 38 families did not answer to our calls. From the 44 subjects assessed neuropsychologically, 3 children did not meet inclusion criteria for cognitive impairment, and 2 did not perform the MRI assessment. A total of 39 children were therefore randomly assigned to one of the training groups (88.6% of the ones who consented). To date, there are 22 children with a baseline visit in the experimental group and 17 in the control group. From those, 26 children to date completed the training (task completion more than 70%) and have both neuropsychological and MRI post-treatment assessments (66.6%). Five children more underwent only neuropsychological assessment (a total of 79.5%) due to claustrophobia or because of MRI abnormalities. A total of eight children (20.5%) dropped out or did not reach the minimum training requirements (at least a 70% of completion), six in the experimental group and two in the control group. We explain this higher dropout rate in the experimental group due to the increasing difficulty in the training tasks. This results in a 79.5% retention rate with a training completion of at least 70%.

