### Discontinuation

A patient may withdraw from the study at any time, at his or her parents' request, for any reason without penalty or loss of benefits. In any case, all patients will be followed up at each assessment time point after discontinuation according to the intention-to-treat principle. In the event of withdrawal of consent, data will be deleted if requested.

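### The MRI missing-data rule removes the whole child rather than the unusable scan, so read literally it discards usable scans from other visits or sequences

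*Protocol article*

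**What the plan says.** The missing-data section treats the two kinds of outcome differently. For behavioural outcomes, "Missing behavioral data can be handled by multiple imputation". For imaging data that are missing, incomplete or artefacted, "we will discard these subjects from the group analysis". The unit removed is the subject, and neither the visit nor the sequence is mentioned. On missed training sessions, the same section adds under an intention-to-treat label that "we will analyze the available data by list-wise deletion without imputing the unknown values".

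Connectivity Changes: MRI Assessment schedules a scan at T0, T1 and T2, derives connectivity from DTI and resting-state fMRI, and calls it a primary measure. Imaging Data says "we need to preprocess MPRAGE, fMRI, and DTI data sets altogether", then describes a DTI analysis in FSL and a functional analysis in FSL and AFNI as separate streams.

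Details of the Sample Enrollment to Date reports 39 children randomised, of whom 26 have both neuropsychological and MRI assessments after treatment.

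**The concern.** Each child can contribute up to six connectivity acquisitions: three visits by two sequences. A rule that acts on the child lets one bad acquisition cancel the other five. Two cases matter:

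- a child with usable T0 and T1 scans who is not scanned, or not scanned cleanly, at 12 months. This child can fully support the post-training contrast;
- a child whose DTI is spoiled but whose resting-state fMRI is sound, or the reverse. This child can fully support one of the two modality-specific analyses.

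What is at stake is precision on a listed primary measure in a very small sample. The imaging result would also be restricted to children scanned cleanly at every visit, who may not represent those randomised. Nothing has to be imputed to avoid this, because the scans in question already exist.

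**Working it through.** **Inputs from the protocol article.** Randomised 39; with T1 neuropsychology and MRI 26; target 30 completers, 15 per group (Sample Size); three MRI visits; two connectivity sequences; two-sided 5% level.

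**Reproducing the stated figure.** 26/39 = 66.7%, given as 66.6% (truncated). The enrolment counts add up: 26 + 5 + 8 = 39. The sample size rests on precedent studies, so there is no power formula to reproduce.

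**Assumed input.** The documents give neither a scan-failure rate nor MRI attrition at T2. Ranges are used below.

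**1. T2 scan missing, literal rule, effect on the T0-T1 contrast.** Children kept = 26 × (1 − f). Interval ratio = √(26 / children kept).

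- f = 10%: 26 × 0.9 = 23.4; √(26/23.4) = 1.054
- f = 30%: 26 × 0.7 = 18.2; √(26/18.2) = 1.195

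The interval is therefore about 5% to 20% wider. Excluding at scan level loses none of these T0-T1 pairs.

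**2. Cross-check with a longitudinal model.** Assume 13 children per arm (the split of the 26 is not given), a common baseline mean, and compound symmetry with correlation 0.5 or 0.7. Compare whole-child deletion with use of all available scans when m children per arm lack only T2. The T1 ratio is the same at both correlations and equals √(13/(13 − m)).

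| m of 13 per arm | SE ratio, T1 effect | SE ratio, T2 effect (correlation 0.5; 0.7) |
|---|---|---|
| 2 | √(13/11) = 1.087 | 1.009; 1.013 |
| 3 | √(13/10) = 1.140 | 1.013; 1.020 |
| 4 | √(13/9) = 1.202 | 1.018; 1.027 |

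The gain is almost all in the post-training contrast. The 1-year contrast gains only 1-3%. In the same model, adding children who have a baseline scan only leaves the SE unchanged (ratio 1.00).

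**3. Any failure in either sequence at any visit.** Assume 30 children and an independent failure probability q per sequence and visit. The literal rule keeps 30 × (1 − q)^6. A single-sequence T0-T1 contrast needs only 30 × (1 − q)^2. The interval ratio is 1/(1 − q)^2.

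| q | literal rule | one sequence, T0 and T1 | interval ratio |
|---|---|---|---|
| 3% | 25.0 | 28.2 | 1.06 |
| 5% | 22.1 | 27.1 | 1.11 |
| 10% | 15.9 | 24.3 | 1.23 |
| 15% | 11.3 | 21.7 | 1.38 |

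In practice failures cluster within children (movement, claustrophobia), so independence overstates this loss. The table shows how the rule compounds and is not a forecast.

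**4. What the loss means at this size.** For one unadjusted two-sided 5% t-test at 80% power, the detectable standardised difference is 1.145 with 13 per arm and 1.407 with 9 per arm (about the f = 30% case). Correction for multiple comparisons makes both worse.

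**The case against.** **The narrower reading.** The strongest reply is that the group analysis is not defined, and may mean only the analysis for which the scan is missing. The Dissemination Policy lists the post-training MRI effects and the 1-year effects as separate reports, and Sample Size defines a complete case by the post-treatment MRI with no T2 condition. On that reading the fall from 26 to between 23 and 18 does not happen. This stands as a plausible intent, but it is not what the rule says, and an analyst applying the text literally would drop the child.

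**Joint processing.** Some planned analyses combine sequences, and a child who lacks one of them cannot enter those. This stands in full. It does not justify removing the child from an analysis that uses only the sound sequence.

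**Condensed article.** Scan-level quality control is commonly left to a fuller document. But the article does not leave this open: it states an exclusion rule, and the rule is too broad.

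**Readings that go too far.** A reader might infer that the cost is already visible, since "Five children more underwent only neuropsychological assessment" (5 of 31 training completers, 16%). The documents do not support that: without a T1 scan no rule can restore the T0-T1 contrast, and a baseline scan alone adds nothing to it. A reader might also take the 6 of 22 against 2 of 17 as evidence of unequal MRI loss. Those children dropped out or trained below 70%; they are not scan failures, and the five without a T1 MRI are not split by arm. Finally, the statement in Discontinuation that "all patients will be followed up at each assessment time point after discontinuation according to the intention-to-treat principle" concerns collecting data. It fits poorly with discarding valid scans, but it does not oblige every imaging analysis to include every child.

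**Conclusion.** The point holds as a badly drawn rule. The text excludes children where it need only exclude scans, on a primary measure. Read literally, it loses valid T0-T1 pairs and valid single-modality data. The size cannot be fixed from the documents: a 5-20% wider T0-T1 interval follows if 10-30% of the 26 children have no usable T2 scan, and that range is an assumption. If the sponsor meant exclusion only from the affected analysis, the T2-related loss is nil and the remedy is one clarifying sentence. The rule concerns the imaging analysis; nothing in it says that a child's behavioural data are dropped. The documents do not show that differential MRI loss between arms has occurred.

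**What to change.** Replace the rule with one that works at scan level:

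- exclude only the unusable scan, for that visit and modality, with usability judged blind to arm;
- keep the child in every planned contrast for which the needed scans are usable, noting that a multi-sequence analysis still needs all its sequences;
- report the numbers analysed by visit, modality and arm;
- keep the set with all visits complete as a sensitivity analysis.

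Where per-child connectivity summaries (edge, graph or tract measures) are analysed over three visits, a mixed model with arm, visit and their interaction on all usable scans can be used. It would stand alongside the planned voxelwise general linear model, TBSS and ICA, not in place of them. Linear mixed models are already planned for food choice and R is already named, so no new data or software are needed.

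The cost is a few sentences of analysis wording and a blinded usability log. The downside is that numbers will differ between contrasts and must be shown with each result.

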#### Sample Size

We attempt to achieve a total sample size of 30 subjects who have completed the treatment (training rate >70% of the days) and with a complete neuropsychological and MRI post-treatment assessment, 15 children per group. Previous literature on the field has shown significant results with similar sample sizes. Boutelle et al. (34) described a significant decrease in the percentage of eating (*d*_ppc2_ = 0.6, medium effect size) and ingested kcal (*d*_ppc2_ = 0.64, medium size), after training attention in a sample of 14 children (vs. 15 children doing a control task), showing far-transfer effect. Also, Verbeken et al. (35) reported a reduction in BMI (at 2-month follow-up; η_p_2 = 0.16, *d*_ppc2_ = 0.20, small effect) and improvement in short-term visual memory (Corsi block tapping task-forward; η_p_2 = 0.13, *d*_ppc2_ = 0.75, large effect), visual working memory (Corsi block-backwards; η_p_2 = 0.14, *d*_ppc2_ = 0.53, medium effect; BRIEF working memory; η_p_2 = 0.10, *d*_ppc2_ = 0.22), and meta-cognition (BRIEF; η_p_2 = 0.12, *d*_ppc2_ = 0.71) after training 22 children with obesity in visual working memory (vs. 22 children in passive control group). Also, Verbeken et al. (36) showed that an inhibition control and attentional training could significantly reduce inhibition problems (BRIEF; η_p_2 = 0.26, *d*_ppc2_ = 1.91, large effect) in a sample of 22 children with obesity (vs. 15 children in the passive control group).

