### Data Analysis Plan

#### Demographic, Neuropsychological, and QoL Variables

For demographic variables, we will use a descriptive analysis of the variables and a comparative analysis between the training and control groups at baseline. We will use the χ^2^ test (and if this is not applicable, Fisher's exact) for categorical variables and Student's *t*-test (if not applicable, the Mann–Whitney *U*-test) for quantitative variables to check that randomization has successfully distributed the possible confounding variables (age, sex, IQ, manual dominance, socioeconomic, and educational status).

For the evaluation of the effectiveness of treatment on BMI and cognition, we will perform a general linear model for repeated measures analysis including these two variables as primary outcomes. We will perform further *post-hoc* analysis evaluating the effects on cognitive domains and emotional and QoL measures if appropriate. Means comparisons will be performed by Student's *t*-test, if the conditions of application are met and confounding variables have been well-controlled (otherwise, adjusted analyses will be performed by multiple regression). Multiple comparisons will be tested by Bonferroni correction. Effect size will also be calculated according to Hunter and Schmidt (58). All statistical tests will be carried using a two-sided test with the significance level set at 5% with the software Statistical Package for the Social Sciences (SPSS, version 24.0) or R (version 3.6.3).

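### The analysis labelled intention-to-treat is list-wise deletion, which is a complete-case analysis, and the article does not say whether deletion or multiple imputation governs BMI and cognition

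*Protocol article*

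**What the plan says.** The relevant text is in the protocol article, mainly under Additional Analysis: Non-adherence or Missing Data.

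- For behavioural outcomes: "Missing behavioral data can be handled by multiple imputation".
- For imaging there is a separate rule: "in the case of missing, uncompleted, or artifacted MRI data, we will discard these subjects from the group analysis".
- A new paragraph then turns to adherence: "Missed trainings will be addressed by an intention-to-treat (ITT) approach to evaluate if they affect the results". The next sentence draws the consequence: "Thus, we will analyze the available data by list-wise deletion without imputing the unknown values".

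Two other sections bear on this. Under Demographic, Neuropsychological, and QoL Variables, the model for BMI and cognition is given as "we will perform a general linear model for repeated measures analysis including these two variables as primary outcomes", and the Outcomes section sets three assessments (T0, T1, T2). Under Discontinuation, the article promises that "all patients will be followed up at each assessment time point after discontinuation according to the intention-to-treat principle".

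**The concern.** Intention-to-treat means that every randomised child is analysed in the allocated group, whatever training was completed. List-wise deletion removes randomised children because of something that happened after randomisation, namely a missing value. The article joins the two with a connecting word, as if one followed from the other.

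Three things are at stake.

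- **Which rule applies.** Imputing and not imputing cannot both be the rule for the same outcome. In a trial of about 39 children, leaving this open allows the choice to be made after results are seen.
- **Use of collected data.** Follow-up after discontinuation has value only if the analysis uses partial records. A three-visit complete-case model does not.
- **Comparability of groups.** The article attributes the higher experimental-group dropout to the rising difficulty of the tasks. If that is right, missingness could be related to treatment and to cognitive performance, and deletion could leave groups that are no longer comparable.

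**Working it through.** **1. The rules side by side**

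| Section | Applies to | Rule |
|---|---|---|
| Non-adherence or Missing Data, first paragraph | missing behavioural data | multiple imputation, worded as permitted |
| Same section, second paragraph | missed trainings, called ITT | list-wise deletion, no imputation |
| Discontinuation | all patients | followed at every time point, under ITT |
| Demographic, Neuropsychological, and QoL Variables | BMI and cognition | repeated-measures general linear model, no missing-data rule stated |

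The first two rows conflict wherever a child who missed trainings also has a missing behavioural outcome. No row settles the last one.

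**2. What deletion does with three visits**

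Take a child seen at T0 and T1 but not at T2. If list-wise deletion is applied in a model of all three visits, it uses none of the child's two observed visits. A mixed model on available data uses both. A discontinued child who attends all three visits is kept under either method, so the harm falls on partial records.

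**3. The article's own counts reproduced** (Details of the Sample Enrollment to Date)

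- Randomised: 22 + 17 = 39.
- Trained and with both post-treatment assessments: 26. With neuropsychological assessment only: 5. Dropped out or under-trained: 8. Sum: 26 + 5 + 8 = 39.
- Non-completion: 8/39 = 20.5%. Retention: 31/39 = 79.5%. Both match the article.

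**4. By group**

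- Experimental: 6/22 = 27.3%. Control: 2/17 = 11.8%.
- Difference: 15.5 percentage points.
- Standard error: √(0.273 × 0.727/22 + 0.118 × 0.882/17) = 0.123.
- Wald 95% interval: 15.5 ± 1.96 × 12.3, that is −8.6 to 39.6 points.
- Odds ratio: (6 × 15)/(16 × 2) = 2.8. Fisher's exact p = 0.43.

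**5. How many children deletion could remove at T1**

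The eight combine dropouts with children who trained below the 70% threshold, and an under-trained child who attended is not deleted. Let m be the number of the eight without T1 data. Then 39 − m remain:

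- m = 0: 39 children (22 vs 17).
- m = 8: 31 children (16 vs 15).

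So at least 26 + 5 = 31 of 39 have T1 neuropsychological data. No T2 attendance is reported, so the further loss at T2 cannot be calculated.

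**6. Possible bias, under assumption**

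Suppose all eight lack data and deleted children differ from retained ones by D standard deviations, equally in both groups. Within a group, the retained mean differs from the full-group mean by D × (proportion deleted). The between-group bias is therefore D × (0.273 − 0.118):

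- D = 0.25: 0.04 SD
- D = 0.50: 0.08 SD
- D = 1.00: 0.16 SD

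D is not in the article. With m = 0 the T1 bias from this source is zero.

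**The case against.** The strongest defence is that the list-wise sentence was never meant for the main analysis. It stands under a heading for additional analyses, its subject is missed trainings, and its purpose is to see whether they affect the results. On that reading, imputation handles missing outcomes, and the second paragraph adds a check that keeps under-trained children who have data. This is plausible and limits the point. It does not remove it: no sentence says so, the imputation is only permitted, and list-wise deletion is not intention-to-treat on either reading.

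Four stronger readings are tempting, and the article does not support them.

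- **That 27% and 12% are rates of lost data.** They are rates of dropping out or under-training, and therefore upper bounds on T1 loss to date. They also rest on eight events and are compatible with chance.
- **That only 26 of 39 would remain for behavioural outcomes.** The article's 26 are children with both neuropsychological and MRI post-treatment assessments. Five more have the neuropsychological data. Reaching 26 for behavioural outcomes would require inventing five T2 losses on top of losing all eight.
- **That deletion biases the effect by a known amount.** Any figure needs a dropout mechanism and T2 losses that are not reported. A gain in precision from a baseline-adjusted mixed model would also come partly from the adjustment, not from retaining children.
- **That a child missing T2 is certain to be lost from the T1 result.** This follows only if one complete-case model spans all three visits. The Dissemination Policy plans separate reports of post-training and one-year effects, so T1 may be analysed alone.

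**Conclusion.** The point holds as an error of definition and an unresolved conflict between rules. A complete-case analysis carries the intention-to-treat label, and the missing-data rule for BMI and cognition cannot be determined from the article.

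The consequence for the result is conditional. To date, deletion would remove between 0 and 8 of 39 children at T1. In the worst case it would take more than twice the share from the experimental group as from the control group. The bias of 0.04 to 0.16 SD belongs to that worst case and to assumed differences of 0.25 to 1.0 SD between deleted and retained children; it illustrates scale and is not an estimate. Loss at T2 is unknown. The case for correction rests on the wording and on the authors' own explanation of the dropout, not on a demonstrated bias.

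**What to change.** 1. Define the intention-to-treat analysis as all randomised children, analysed in their allocated group regardless of training completion.
2. For BMI and global cognition, name one primary method: a linear mixed model on all available visits with the baseline value taken into account, or multiple imputation. Make the other the sensitivity analysis. The Food Choice section already plans linear mixed models, so the first option lies within the team's stated methods.
3. Relabel the list-wise analysis as a supplementary complete-case analysis.
4. When reporting, separate children with no post-training visit from under-trained children who attended, by group and by visit, so that the real data loss can be seen.

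The cost is analysis wording and a little more analysis work, with no new data. The one real drawback is that both methods rely on data being missing at random given what was observed. That should be stated as an assumption.
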